##### Cost-effectiveness evaluation

Using a health services perspective, incremental cost-effectiveness ratios will be calculated from the cost per person quit in the intervention phase (i.e. self-reported 6-month abstinence from smoking) compared to usual care in the pre-intervention phase. Costs for the delivery of the intervention (e.g. clinician training, smoking cessation resources, NRT/pharmacotherapy where appropriate) will be derived directly from trial data and added to the costs of clinician time (e.g. oncology nurses) in usual care. Exploratory, modelled analyses will examine the potential impacts of smoking cessation (intervention versus usual care) on the cost per quality adjusted life year saved, using mortality relative risk estimates derived from published studies of survival by post-diagnosis smoking cessation (however these studies are likely subject to confounding by indication for quitting and as such modelled results based on these data will be interpreted cautiously). Modelled analyses will include estimates of the health-system costs of cancer [59] and health state utilities for cancer survivors [60]. Sensitivity analyses will address potential variation in costs and the survival benefits due to smoking cessation.

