### Primary hypotheses

1a) The proportion of smokers and recent quitters receiving anti-cancer therapy who achieve self-reported 6-month prolonged abstinence from smoking will be higher post-intervention compared to pre-intervention (14% vs. 7%).

1b) Biochemically verified 7-day point-prevalence abstinence from smoking at 7 months post-recruitment will be higher after the intervention phase than at the baseline phase (25% vs. 15%).

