#### Cost effectiveness

Cost effectiveness will be measured by cost per successful quit attempt from a service-provider perspective. These data will be sourced from project and site records.

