### Evaluation

#### Statistical methods

Independent and blinded statisticians from the CReDITSS Unit at the Hunter Medical Research Institute, Australia, supervised by CI [name], will conduct analyses of the primary and secondary outcomes.

Logistic regression within a generalised linear mixed models framework will be used to model the primary and secondary outcome measures. All models will adjust for time using a fixed effect that describes the phase of the study (pre-intervention and each of the 3 steps). Variation between sites will be accounted for using a random effect for site and repeated measures on sites will be accounted for using a random effect for time within site. To estimate the intervention effect, a variable indicating when the intervention was active for a given site and time will be included in the models. As the timing of the 7 month CATI for some participants overlaps with intervention commencement, the analyses of 6 months abstinence will include a 6-month offset to the coding of the intervention indicator variable to allow the full effect of the intervention to be in place before estimating its effect.

There are no plans for interim analyses.

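### The cost-effectiveness ratio is defined as intervention phase against pre-intervention phase and is not tied to the time-adjusted effect, so a calendar trend in quitting would enter it

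*Protocol article*

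**What the plan says.** Under Cost-effectiveness evaluation, the protocol article states that "incremental cost-effectiveness ratios will be calculated from the cost per person quit in the intervention phase", with a quit taken as self-reported 6-month abstinence, and that this is "compared to usual care in the pre-intervention phase". The sensitivity analyses named there are limited: "Sensitivity analyses will address potential variation in costs and the survival benefits due to smoking cessation".

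Under Statistical methods, the plan for effectiveness is different in kind: "Logistic regression within a generalised linear mixed models framework will be used to model the primary and secondary outcome measures". It adds: "All models will adjust for time using a fixed effect that describes the phase of the study". For 6-month abstinence the intervention indicator is also shifted by six months.

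Under Secondary outcomes, the short Cost effectiveness entry words the measure in another way: "Cost effectiveness will be measured by cost per successful quit attempt from a service-provider perspective".

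Cost effectiveness is the third stated aim and is hypothesis 3. The Discussion says the result is meant for governments that commission or fund care.

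**The concern.** In a stepped wedge, exposure to the intervention rises with calendar time by design. That is why the outcome models carry a fixed effect for time. The economic section names two phases and compares them, without saying that the difference in quits comes from those models.

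The general modelling sentence does not close the gap. A logistic mixed model gives an odds ratio, whereas a cost per extra quit needs an absolute difference in the probability of quitting. Some conversion step is required and none is named. An analyst who follows the economic section literally would use phase proportions, and any trend in quitting unrelated to the intervention would go into the ratio.

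Two analysts could then report different ratios from the same data. The economic conclusion could also disagree with the trial's own effect estimate: if the adjusted effect were nil, a rising trend alone would still produce a finite cost per quit.

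**Working it through.** **Inputs from the protocol article.** Recruitment is 40 per site per 6 months over 3 years at nine sites (Sample size). Sites start the intervention at months 6, 13 and 19, three sites at a time (Implementation of Care to Quit). Implementation lasts 12 months. Abstinence is 7% before and 14% after (hypothesis 1a), a difference of 7 points.

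**Assumptions.** Recruitment is even over 36 months; the secular trend in 6-month abstinence is linear; incremental cost is unaffected by the trend. The documents give no trend, so 0.5, 1 and 2 points a year are illustrative.

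**Plan's own figure.** 40 × 6 × 9 = 2160, as stated. The economic section gives no figure of its own. Three sites together recruit 3 × 40 / 6 = 20 patients a month.

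**Control patients.** Control time is 6 + 13 + 19 = 38 months over the three groups of sites, so 38 × 20 = 760 patients. Mean recruitment month = (6×3 + 13×6.5 + 19×9.5) / 38 = 283 / 38 = 7.4.

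**Intervention patients, three readings of the phase.**
- The 12 months after each start: midpoints 12, 19 and 25, 720 patients, mean (12 + 19 + 25) / 3 = 18.7. Gap 11.2 months = 0.935 years.
- Everyone after start: 30 + 23 + 17 = 70 group-months, 1400 patients, mean (30×21 + 23×24.5 + 17×27.5) / 70 = 1661 / 70 = 23.7. Gap 16.3 months = 1.357 years.
- Implementation year left out: 18 + 11 + 5 = 34 group-months, mean (18×27 + 11×30.5 + 5×33.5) / 34 = 989 / 34 = 29.1. Gap 21.6 months, about 22. With starts rounded to 6, 12 and 18 the gap is 22.0.

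**Concurrent overlap.** Controls recruited after month 6, when the first three sites have started, number (7 + 13) × 20 = 400 of 760, or 53%.

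**Bias.** With trend *d* points a year and gap *g* years, the crude difference is 7 + *g·d*. At unchanged incremental cost, the cost per extra quit is understated by 1 − 7 / (7 + *g·d*).

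| Trend (points/year, assumed) | Gap 11.2 months: crude difference, understatement | Gap 16.3 months: crude difference, understatement |
|---|---|---|
| 0 | 7.0, none | 7.0, none |
| 0.5 | 7.5, 6% | 7.7, 9% |
| 1 | 7.9, 12% | 8.4, 16% |
| 2 | 8.9, 21% | 9.7, 28% |

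A fall of 1 point a year with the 16.3-month gap gives 7 − 1.36 = 5.64 points. The cost per extra quit is then overstated by 7 / 5.64 − 1 = 24%. If the true effect is nil, the crude gain with that gap is trend only: 0.7, 1.4 or 2.7 points for the three assumed rises.

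**Does time adjustment remove it?** On a grid of six 6-month periods with starts at 6, 12 and 18 months, a fit with period effects returned 7.0 points when the truth was 7, and 0 when it was 0, for each of the three trends. This used six period effects and a linear scale, not the plan's four-level phase factor and logistic model.

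**The case against.** A reader might infer that the economic analysis is a plain before-after comparison that ignores calendar time and discards the randomised order. The documents do not support that.

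- The section never says raw, crude or unadjusted. Hypothesis 1a uses similar pre/post shorthand for abstinence, and that outcome is analysed with time adjustment. Cost effectiveness is also listed among the secondary outcomes, and its quit measure corresponds to the primary outcome, so the authors may intend the adjusted effect to feed the ratio.
- Controls are not all recruited early: more than half enter while other sites are already in intervention.
- The size depends on an assumed trend and on what intervention phase means. Table 2 separates a 12-month intervention period from a post-intervention period, and the gap changes accordingly.
- A reader might also see a contradiction between counting 24-hour quit attempts and counting 6-month abstinence. The 24-hour definition belongs to another outcome, length of quit attempts, and the Cost effectiveness entry says successful attempts. This is loose wording that the later section makes specific.

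All of this stands against the stronger reading. It does not remove the point. The section does fix a contrast, that contrast is by phase, and no sentence ties it to the model estimate or says how an odds ratio becomes a difference in quits. The article may leave detail to an analysis plan, but the rule it does print would mislead if followed.

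**Conclusion.** The point holds as a defect in how the ratio is defined; it does not show that an unadjusted analysis is intended. As written, the ratio contrasts two phases whose patients differ in mean recruitment date by about 11, 16 or 22 months, depending on how the intervention phase is read, and it would take up any secular trend in quitting. The percentages are conditional on trends the documents do not supply, on a true effect of 7 points, on even recruitment and on unchanged incremental cost. One of three stated aims is affected; the primary analysis is not. The point should be corrected, because the result is meant to inform funders and the remedy is small. The wording of the quit measure is a minor matter to align at the same time.

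**What to change.** In Cost-effectiveness evaluation, state that the ratio is incremental cost per patient divided by the marginal risk difference in 6-month prolonged abstinence. Take that difference from the time-adjusted mixed model in Statistical methods, with the same intervention indicator and 6-month offset. Compare costs on the matching groups of patients, and take the uncertainty of the effect from that model. In the Cost effectiveness entry under Secondary outcomes, replace the reference to successful quit attempts with 6-month prolonged abstinence.

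The cost is a few sentences and one conversion from a model already planned; no new data are needed. The interval around the ratio will be wider than one from crude phase proportions.

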### Qualitative evaluation

A nested qualitative study will be conducted. All interviews (key informants and Quitline counsellors) will be audio recorded, transcribed and a general inductive approach will be taken for the analysis [61]. Interviews will be guided by semi-structured interview guides.

#### Key informant interviews

Semi-structured interviews will be conducted with *n* = 45 staff participants (*n* = 5 per site). Potential participants will be purposively selected at each timepoint (baseline, intervention, post-intervention) to be invited for interview. Potential participants will be identified by the site principal investigator in consultation with the research team and advised by the principal investigator that they will be contacted by the research team with an invitation to participate in an interview. Eligible participants will include cancer services directors, heads of departments, directors of cancer nursing and team leaders. Interviews will explore the perceived role of system-level factors (e.g. staffing, leadership, technology, infrastructure) which can affect implementation. The interviews will also evaluate the method of multiple outreach visits in identifying and motivating an interdisciplinary group of champions. Participants will have the option of reviewing the interview transcript and editing their responses prior to analysis.

#### Quitline counsellor interviews

Interviews will evaluate the experience of delivering counselling to study participants amongst Quitline staff. It is anticipated that semi-structured individual and/or group in-depth interviews will be conducted with Quitline counsellors to enable data collection to reach saturation and for key themes to be identified [62]. Interviews will explore their experience of delivering counselling and its strengths and weaknesses from their perspective. Interviews will be conducted face to face, via telephone or videoconference depending on practicality and participant preference. Participants will have the option of reviewing the interview transcript and editing their responses prior to analysis.

Recruitment will be undertaken via email from Quitline managers to all eligible Quitline staff (those that delivered counselling to Care to Quit participants) asking them to participate in an interview. Their participation will be optional.

### Harms

Adverse events will be monitored by study sites (hospitals) as per their usual protocols.

### Protocol amendments

Each study site will only be able to start data collection once the relevant Ethics Committee and research governance approval is obtained. In the case of proposed protocol changes, an amendment will be submitted to the Ethics Committees for approval, and the trial coordinating centre will ensure all study staff are provided with new documentation. Any significant protocol changes will be updated on the ANZCTR site and reported in the final outcomes paper.

### Confidentiality

The trial will be conducted in accordance with applicable Privacy Acts and Regulations. Data that identify any trial participant will not be revealed to anyone not directly involved in the trial or the clinical care of that participant. An exception is where the trial participant has provided written consent for his/her records to be included in source document verification.

### Access to data

All data will be considered the property of the trial chief investigator who, in consultation with the trial management committee, will be responsible for presentations and publications arising from this trial.

### Dissemination policy

Trial findings will be summarized and provided to participants who have indicated they would like a copy of the results. The trial management committee will be responsible for decisions regarding presentations and publications arising from this trial according to agreed Authorship, Publication and Spokesmanship Guidelines.

Access to data during the trial will be limited to the trial management committee and appropriate regulatory bodies.

## Discussion

Given the risks of greater morbidity, tumour recurrence and mortality in the 25% or more of people with cancer who continue to smoke [13, 27], the untapped benefit of achieving smoking cessation amongst people with cancer is substantial. Oncology clinicians and health professionals have a pivotal role to play in delivering best practice smoking cessation care. In addition to the likelihood of successfully improving the implementation of smoking cessation care for people with cancer, the Care to Quit trial will advance the field of implementation science in three ways. Firstly, the initial intervention stage addresses the capability and motivation of staff intensively via outreach visits before study teams are formed. Secondly, outreach visits (personal visits by a trained person to professionals in their own settings) are much less studied than strategies such as feedback. While outreach visits have been found effective for changing prescribing [63], it is not clear whether this approach is effective for changing other aspects of behaviour (e.g. content and nature of consultation advice). Third, champions are assumed as essential but there is little data on how to identify or develop leaders for practice change [64–66]. The cost effectiveness evaluation will provide valuable information for state and national governments that commission or fund health care regarding the costs of upscaling the implementation (should it be effective).

### Limitations

Site clinicians will not be blind to participant allocation, which may introduce bias into their documentation of the provision of smoking cessation care into patient medical records or their own self-report in surveys. However, record audits have been found to be a valid measure of care provision [67] and these will also be supplemented with patient recall of receipt of smoking cessation care.

It would be useful in future studies to follow the participants over a longer timeframe to measure longer-term health and other benefits.

## Data Availability

Not applicable.

## Abbreviations

CATI: Computer-assisted telephone interviews
NRT: Nicotine replacement therapy
QOL: Quality of life
REDCap: Research Electronic Data Capture
SPIRIT: Standard Protocol Items: Recommendations for Interventional Trials
